## Abstract

**Background:**

The optimal vitamin D intake for nursing mothers with overweight or obesity has not been defined. Vitamin D concentrations are associated with body composition indices, particularly body fat mass. Few studies have investigated the relationship between hypovitaminosis D, obesity, anthropometric status, and body composition in nursing women. Thus, the present study aims to investigate whether vitamin D supplementation during lactation will improve vitamin D status, reduce body fat mass, and improve body composition.

**Methods/design:**

In a double-blind, randomized, placebo-controlled, parallel-group trial, after term delivery, 90 healthy women with overweight or obesity will be selected and randomly allocated into three groups to receive 2000 IU/d cholecalciferol (vitamin D3), 4000 IU/d cholecalciferol, or placebo (lactose) for 12 weeks while nursing. Measurements of height, weight, waist circumference, and body composition (fat mass (kg), lean mass (kg), body fat (%), fat mass index, and relative fat mass index) will be taken for all subjects at baseline and after 12 weeks of intervention. In addition, serum 25-hydroxyvitamin D (25(OH)D), parathyroid hormone, calcium, and phosphorus will be measured.

**Discussion:**

This study is the first investigating the effect of different amounts of vitamin D supplementation on serum calcidiol, anthropometric status, and body composition in nursing women with overweight or obesity. Our findings will contribute to the growing body of knowledge regarding the role of vitamin D supplementation in obesity, anthropometric status, and body composition in nursing women.

**Trial registration:**

Iranian Registry of Clinical Trials IRCT20140413017254N6. Registered on 11 April 2018.

**Electronic supplementary material:**

The online version of this article (10.1186/s13063-019-3622-y) contains supplementary material, which is available to authorized users.

## Background

In developed countries, 50% of nursing mothers suffer from overweight or obesity [1]. In Iran, the prevalence of overweight or obesity in nursing women is estimated at 31.7–37.3% [2, 3]. Nursing mothers expend 500 kcal per day for milk production [4], resulting in gradual weight loss [5, 6].

However, factors such as unhealthy dietary intake, low physical activity [7], higher leptin level [8], or pre-pregnancy body mass index (BMI) [9], and deficiency of serum 25-hydroxyvitamin D (25(OH)D; ≤ 20 ng/ml or 50 nmol/l) [10] are associated with more weight gain or obesity during pregnancy, which may lead to chronic diseases in nursing mothers [11].

The global prevalence of vitamin D deficiency (≤ 20 ng/ml) and severe deficiency (≤ 10 ng/ml or 25 nmol/l) in pregnant and nursing women is estimated to be between 21 and 85% [12, 13]. The results of the Second National Survey on the status of micronutrients in Iran showed that 85% of pregnant women are exposed to vitamin D deficiency (≤ 20 ng/ml) or severe deficiency (≤ 10 ng/ml) [14]. Therefore, vitamin D deficiency is also expected to be high in nursing women. On the other hand, some studies have shown a decrease in serum levels of vitamin D during lactation [12, 15]. The retention of vitamin D in body fats due to overweight in pregnancy [16], an increase in the body’s need for bone mass [17], lack of adequate sunlight exposure [18], and very low levels of vitamin D intake are the most significant reasons for deficiency of vitamin D in nursing mothers [19].

Obesity and overweight are among the most important risk factors for vitamin D deficiency [20]. The concentration of 25(OH)D is low in adults with obesity [21] and is inversely related to body weight, BMI, percentage of body fat, and visceral fat [22, 23]. It has been reported that after exposure to sunlight, the increase in serum levels of vitamin D was 57% less in subjects with obesity compared to subjects without obesity. Thus, it has been concluded that the release of vitamin D from the skin into the blood is altered in individuals with obesity [12]. However, another study reported that volumetric dilution of vitamin D in the large adipose tissue causes vitamin D deficiency in individuals with obesity [24].

The Institute of Medicine (IOM) recommended 600 IU vitamin D for nursing women, which is based on the role of vitamin D in bone health, but treating women with obesity may require more amounts of vitamin D. The Endocrine Society guidelines recommend that adults with obesity need two to three times more vitamin D (6000–10,000 IU/d) to treat and prevent vitamin D deficiency [19].

The results of a systematic review reported that findings on the effect of vitamin D supplementation on weight reduction in subjects with overweight and obesity were not conclusive [25]. However, most of the included studies in this review used a combined treatment of vitamin D and other substitutes, making interpretation of the findings more difficult. Another systematic review and meta-analysis reported that 25(OH)D levels are inversely correlated with body fat percentage (BFP), but no effect was found regarding vitamin D supplementation on BFP [26]. However, many included studies in this meta-analysis were not performed specifically in individuals with overweight or obesity and included postmenopausal women or patients with type 2 diabetes mellitus. In addition, some of these studies did not use high doses of vitamin D. On the other hand, a review study concluded that most clinical trials with null effect of vitamin D on health were performed in populations without vitamin D deficiency. So possible beneficial effects from vitamin D supplementation cannot be excluded [27].

To the best of our knowledge, the effect of different doses of vitamin D supplementation on anthropometric status and body composition has not been investigated specifically in nursing women with overweight or obesity. Only one study investigated the effect of vitamin D supplementation on body composition in nursing women with different weight statuses, including women with overweight or obesity. However, data for women with obesity has not been presented separately. Receiving 400 or 1200 IU/d of vitamin D for 6 months has not been found to influence body composition, which is probably due to the low amount of the vitamin. However, an inverse relationship has been reported between serum level of vitamin D and fat mass [28]. Therefore, further studies are needed to determine the appropriate amount of vitamin D for improving vitamin D status and body composition in nursing mothers with overweight or obesity. Thus, we proposed to start a randomized controlled trial with the following objectives:
i.To investigate whether vitamin D supplementation can improve anthropometric status and body composition in nursing women with overweight or obesityii.To investigate whether vitamin D supplements can improve the vitamin D status of these womeniii.To investigate what amount of vitamin D supplementation can reduce the serum level of parathyroid hormone (PTH) in these women

## Methods/design

### Study design

Subjects will be randomly assigned into groups with a 1:1:1 randomization ratio. A flow chart of the study protocol is presented in Fig. 1.

**Fig. 1 Fig1:**
[figure not shown]
Recruitment flow chart

Four types of questionnaires will be completed by each subject at the beginning and end of the study: socio demographic, 24-h recalls to collect dietary intake data, sunlight exposure questionnaire, and physical activity questionnaire (International Physical Activity Questionnaires (IPAQ)).

The necessary information on anthropometric measurements (height, weight, BMI, body fat percentage, body weight (kg), lean mass (kg), visceral fat, and visceral fat mass (kg), relative fat mass index (RFM), fat mass index (FMI) will be obtained using In Body model 270 as a body composition analyzer (In Body Co., Ltd, Seoul, Korea). Serum levels of vitamin D, PTH, as well as calcium and phosphorus levels will be measured at the beginning and end of intervention. Table 1 shows the primary and secondary outcome measures and the time for measurement and a Standard Protocol Items: Recommendations for Interventional Trials (SPIRIT) checklist is included as Additional file 1. The anthropometric and body composition measures, including height, weight, BMI, body fat percentage, body weight, lean mass, visceral fat and visceral fat mass, RFM, and FMI were intended to be primary outcomes but were unintentionally omitted in the preregistration. However, our sample size calculation is based on waist circumference as intended as a primary measure.

**Table 1 Tab1:** Outcome measures and measurement times

	Months	
	0	3
Primary outcomes		
Blood analysis		
Serum 25(OH)D	*	*
Serum PTH	*	*
Serum calcium	*	*
Serum phosphor	*	*
Anthropometry and clinical assessment		
Height (cm), weight (kg)	* *	*
Body mass index (kg/m^2^)	*	*
Waist circumference (cm)	*	*
Body composition		
Fat mass (kg)	*	*
Lean mass (kg)	*	*
Body fat (%)	*	*
Visceral fat mass (kg)	*	*
Fat mass index (FMI)	*	*
Relative fat mass index (RFM)	*	*
Secondary outcomes		
Weight (kg), height (cm), head circumference (cm), of the infants	*	*
Infection frequency in infants		*
Frequency of doctor visits		*

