### Sample size estimation

Sample size was calculated according to Roosta et al. [29] using two mean comparison formula. In this formula, considering α = 0.05, β = 0.2, and mean (standard deviation) of waist circumference changes after supplementation with vitamin D, which was equal to 1.91 cm (1.7) and 0.55 cm (1.04), respectively, in the intervention and control groups, sample size is estimated as 18 subjects. Since, there are three groups in this study, the calculated sample size was multiplied with $$ \sqrt{number\ of\ groups} $$, and finally the desired sample size for this study was obtained as 90 subjects (30 subjects per group).

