### Statistical analysis

Missing data will be imputed using the regression imputation method. Quantitative variables will be reported as mean (standard deviation) and qualitative variables will be reported as percentages. ANOVA and Chi-square tests will be used to compare quantitative and qualitative variables in the three groups. To evaluate the effect of vitamin D supplementation on visceral fat mass, visceral fat percentage, lean mass, body fat percentage, waist circumference, FMI, RFM, BMI, and biochemical factors such as serum 25(OH)D, PTH, calcium and phosphorus levels two-way Repeated Measures ANOVA (RMA) will be applied in SPSS software version 21 (SPSS Inc., Chicago, USA). RMA assesses whether the mean changes in the results from baseline to 12 weeks differ in the three groups. This statistical analysis measures time to group interaction term. There are no planned interim analyses. The 95% confidence level will be considered.

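### Fourteen variables are labelled primary, only waist circumference is sized, no outcome is named as decisive, and the analysis list does not match the outcome table

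*Protocol article*

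**What the plan says.** **Outcome table.** Table 1 (Study design) lists as primary:
- four blood measures: serum 25(OH)D, PTH, calcium, phosphorus;
- four anthropometric measures: height, weight, BMI, waist circumference;
- six body composition measures: fat mass, lean mass, body fat %, visceral fat mass, FMI, RFM.

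That makes 14. The only secondary outcomes concern the infants and doctor visits. The text above the table says of the body measures that they "were intended to be primary outcomes but were unintentionally omitted in the preregistration", and adds: "However, our sample size calculation is based on waist circumference as intended as a primary measure".

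**Sizing.** The Sample size estimation section works from waist circumference alone, "considering α = 0.05, β = 0.2", with changes "equal to 1.91 cm (1.7) and 0.55 cm (1.04), respectively, in the intervention and control groups".

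**Analysis.** The Statistical analysis section applies a two-way repeated measures ANOVA to a named list that begins "To evaluate the effect of vitamin D supplementation on visceral fat mass, visceral fat percentage, lean mass, body fat percentage, waist circumference, FMI, RFM" and goes on to BMI and the four blood measures, 12 variables in all. The only error statement is "The 95% confidence level will be considered".

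**Aim.** The abstract's background says the trial will examine whether supplementation will "reduce body fat mass, and improve body composition".

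**The concern.** A trial sized for one outcome at 5% has that error rate only if that outcome decides the result. Here waist circumference is one primary among 14 with no special standing. Any of the listed tests reaching p < 0.05 could be reported as a positive primary result. That includes a change in a blood measure, which would say nothing about body composition.

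The mismatch between the lists adds to the freedom of choice. A reader cannot tell whether fat mass in kilograms, the quantity named in the aim, is itself to be tested or only its height-scaled form. Nor can the reader tell what visceral fat percentage is. Because the body measures were left out of the registration, the protocol is the main record of what was decided in advance, and it does not settle the matter.

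**Working it through.** **1. The plan's own sample size.** From Sample size estimation: difference 1.91 − 0.55 = 1.36 cm; SDs 1.7 and 1.04; alpha 0.05 (taken as two-sided, since the sidedness is not stated); power 80%.

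n per group = (1.7² + 1.04²)(1.960 + 0.842)² / 1.36² = 3.9716 × 7.849 / 1.8496 = 16.85, or 17. The t-based version gives 18, which agrees with "sample size is estimated as 18 subjects". Then 16.85 × √3 = 29.2 (or 17 × √3 = 29.4), rounded up to 30 per group, 90 in total. Starting from the rounded 18 would give 31.2, but the figure of 90 reproduces from 16.85 or 17. It is a calculation for one outcome at the full 5%.

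**2. The two lists side by side.**

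| | Variables |
|---|---|
| In both (11) | 25(OH)D, PTH, calcium, phosphorus, BMI, waist, lean mass, body fat %, visceral fat mass, FMI, RFM |
| Table 1 only (3) | fat mass (kg), weight, height |
| Analysis list only (1) | visceral fat percentage |

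The Study design text mentions an unqualified visceral fat item beside visceral fat mass, without unit or definition. The Anthropometry and body composition section describes neither.

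**3. Chance of at least one false positive, each test at 5%, no true effects.**
- 12 listed tests, independent: 1 − 0.95¹² = 0.460.
- If one of the 12 is set aside, whether visceral fat percentage (not in Table 1) or 25(OH)D (because it truly rises): 1 − 0.95¹¹ = 0.431.
- The four blood tests alone: 1 − 0.95⁴ = 0.185.

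The body measures are correlated, and the documents give no correlations. Simulating 12 equicorrelated normal statistics under assumed values:

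| Common correlation | 0 | 0.3 | 0.5 | 0.7 | 0.9 |
|---|---|---|---|---|---|
| Chance of ≥ 1 false positive | 46% | 40% | 32% | 23% | 13% |

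These count one test per outcome. Dose-versus-placebo contrasts would add to them.

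**4. Power for waist, one primary against 14.** Pooled SD = √(3.9716/2) = 1.409, so the standardised difference is 1.36/1.409 = 0.965. The 10% maximum dropout (Strengths and limitations) leaves 30 × 0.9 = 27 per group.

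*One pairwise t test.* Noncentrality = 1.36 / (1.409 × √(2/27)) = 3.546 on 52 degrees of freedom. Power is 93.6% at 0.05 and 68.7% at 0.05/14 = 0.00357. With 30 per group the Bonferroni figure is 75.4%.

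*The planned three-group test.* With two time points, the time-by-group interaction equals a one-way ANOVA on change scores. The noncentrality is λ = 27 × Σ(group mean − grand mean)² / 1.409² on 2 and 78 degrees of freedom. The middle group's mean is not given, so it is varied between the other two:

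| Middle group | λ | Power at 0.05 | Power at 0.05/14 |
|---|---|---|---|
| Equal to either extreme | 27 × 1.2331 / 1.9858 = 16.77 | 96% | 77% |
| Halfway | 27 × 0.9248 / 1.9858 = 12.57 | 89% | 58% |

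**The case against.** **Fat mass and weight are not really left untested.** FMI and BMI are fat mass and weight divided by height squared, and height is essentially fixed in adults. Both are in the analysis list, as is body fat %. A general sentence also says ANOVA will compare quantitative variables across groups. This stands. A reader might infer that the headline aim has no planned test, and the document does not support that. What remains is that two measures labelled primary are not named in the efficacy analysis.

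**Visceral fat percentage may be an intended outcome.** The Study design text twice lists visceral fat separately from visceral fat mass, so the percentage may be that item. This stands too. A reader might conclude that it should be deleted, but the document supports only defining and reconciling it.

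**A multiplicity rule may sit in an analysis plan that is not shown.** It may, and silence on adjustment alone would be a weak point. But the article itself fixes 14 primaries, sizing for one of them at the full 5%, and an analysis list that disagrees with its table. An unseen rule would not reconcile these.

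**The error rate is an upper bound.** Partly so. A figure of 51% (1 − 0.95¹⁴) is tempting, but it counts height, which is not on the test list, and it ignores correlation. The range in the working allows for both and stays above 5% throughout.

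**Three objectives are stated, so a single family of tests is not self-evident.** That is fair, and it is why 25(OH)D could reasonably stay primary beside a body outcome. It does not justify several undifferentiated body primaries.

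**The registration omission.** The authors disclose it and call it unintentional. A reader might infer outcome switching, but nothing in the document supports that, and the registry record is not at hand.

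**Conclusion.** The point holds. The protocol does not define which result makes the trial positive, and its outcome table and analysis list need reconciling. Followed as written, the chance of at least one false positive among the 12 listed tests is 46% under independence and about 40% to 13% for assumed common correlations of 0.3 to 0.9. This rests on one test per outcome, no true effects and an equal-correlation model, because the documents give no correlations.

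The sample size itself is not at fault: it suits waist as a single primary. At the stated effect and 27 per group, one pairwise test on waist has about 94% power at 5%, against about 69% if all 14 stayed primary under Bonferroni. For the planned three-group test the ranges are 89–96% and 58–77%. The protocol does not propose Bonferroni; the comparison only shows what keeping 14 primaries with strict control would cost.

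**What to change.** 1. Name waist circumference, the outcome already sized, as the single confirmatory body outcome at two-sided 5%, and make the other body and blood outcomes secondary. If serum 25(OH)D is also kept as primary for objective ii, prespecify an error-control rule across the two. A fixed sequence is one option; the documents do not require it or a particular order. If the sponsor would rather have fat mass as the confirmatory outcome, the sizing must be redone for it.
2. Remove height as an outcome and keep it as a measurement for BMI and FMI.
3. Add fat mass (kg) and weight to the list in the Statistical analysis section.
4. Define visceral fat percentage and reconcile it with the visceral fat item in the Study design text and with Table 1.
5. Update the registry entry before unblinding.

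The cost is rewording Table 1 and the analysis paragraph, plus a registry update. The downside is that the outcomes made secondary, including fat mass and PTH (objective iii), could support a claim but not establish one.

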### Sample size estimation

Sample size was calculated according to Roosta et al. [29] using two mean comparison formula. In this formula, considering α = 0.05, β = 0.2, and mean (standard deviation) of waist circumference changes after supplementation with vitamin D, which was equal to 1.91 cm (1.7) and 0.55 cm (1.04), respectively, in the intervention and control groups, sample size is estimated as 18 subjects. Since, there are three groups in this study, the calculated sample size was multiplied with $$ \sqrt{number\ of\ groups} $$, and finally the desired sample size for this study was obtained as 90 subjects (30 subjects per group).

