### Strengths and limitations of the study

The strengths of our protocol study include assessing the different doses of vitamin D supplementation to treat vitamin D deficiency in nursing women with BMI of 25 kg/m^2^ and higher.Also, this study is the first study evaluating the effects of different amounts of vitamin D supplementation on anthropometric status and body composition in nursing women with BMI of 25 kg/m^2^ and higher.Body composition measurements are not assessed by gold standard techniques, which can be considered as a limitation of this study.Possible poor cooperation of some patients is another limitation of this study.The calculated sample size is another limitation of this study. Due to financial constraints, the number of subjects is limited to 90. As such, a 10% dropout is considered the maximum.

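### The sample size of 90 does not follow from the printed calculation (18 × √3 = 31.2 per group, not 30), and the power of the planned three-group test is never stated

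*Protocol article*

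**What the plan says.** All of the sizing is in the protocol article, section Sample size estimation. It starts "using two mean comparison formula", "considering α = 0.05, β = 0.2", with "mean (standard deviation) of waist circumference changes after supplementation with vitamin D, which was equal to 1.91 cm (1.7) and 0.55 cm (1.04") in the intervention and control groups. The result is given as "sample size is estimated as 18 subjects". The next step reads "Since, there are three groups in this study, the calculated sample size was multiplied with" the square root of the number of groups, "and finally the desired sample size for this study was obtained as 90 subjects (30 subjects per group").

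Three other places bear on this:

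- **Study design:** "Subjects will be randomly assigned into groups with a 1:1:1 randomization ratio".
- **Statistical analysis:** a two-way repeated measures ANOVA tests whether change from baseline to 12 weeks differs among the three groups (the time-by-group term), at the 95% confidence level.
- **Strengths and limitations of the study:** the sample size is named as a limitation, and "Due to financial constraints, the number of subjects is limited to 90. As such, a 10% dropout is considered the maximum".

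**The concern.** There are three faults in how 90 is justified.

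1. The printed numbers do not connect: 18 multiplied by √3 is not 30.
2. The square-root step has no stated alpha, comparison or power behind it. The 80% power in the text belongs to a two-arm comparison with 18 per arm, whereas the planned analysis is a three-group test.
3. The accepted dropout appears only under limitations and does not enter the calculation.

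The document also gives two accounts of the same number. In one section 90 is the outcome of a calculation; in another it is a budget ceiling. A reader cannot tell which comparison the trial was sized for, or what power it has once losses are allowed for. If the √3 step hid a real shortfall, the main result on waist circumference could be an uninformative null. The power therefore has to be worked out.

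**Working it through.** **Inputs.** All are from the protocol article: alpha 0.05 and beta 0.2; mean changes 1.91 and 0.55 cm; SDs 1.7 and 1.04 cm; allocation 1:1:1; 30 per group; at most 10% dropout. Two assumptions are mine: alpha is two-sided, and 18 means per group. If 18 were a total, the √3 step would give about 31 women in all, nowhere near 90.

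**Step 1: the base of 18.** The difference is 1.91 − 0.55 = 1.36 cm. The variances sum to 1.7² + 1.04² = 3.9716, so the common SD is √(3.9716/2) = 1.409 and the standardised difference is 1.36/1.409 = 0.965.

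- Normal approximation: n = (1.960 + 0.842)² × 3.9716 / 1.36² = 16.85, rounded up to 17 per group.
- t-test: 18 per group gives 80.3% power and 17 gives 77.9%, so the answer is 18. This reproduces the printed figure.

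**Step 2: the multiplier.**

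| Base | × √3 | Rounded up per group | Total |
|---|---|---|---|
| 18 (printed) | 31.18 | 32 | 96 |
| 17 | 29.44 | 30 | 90 |
| 16.85 | 29.19 | 30 | 90 |

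The printed 18 does not give 30. A base of 17 or 16.85 does, but neither is printed.

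**Step 3: dropout.** 30 × 0.9 = 27 completers per group. Nothing in the sizing section allows for this.

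**Step 4: power of the planned test.** With two time points, the time-by-group term is equivalent to a one-way ANOVA on change scores, with 2 and 3n − 3 degrees of freedom. The noncentrality is λ = n × Σ(group mean − overall mean)² / SD². The protocol gives no expected mean for the 2000 IU group, so I took the lowest and highest group means as 1.36 cm apart and let the 2000 IU mean vary:

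- 2000 IU midway: Σ = 2 × 0.68² = 0.925.
- 2000 IU equal to either extreme: Σ = (2/3) × 1.36² = 1.233.

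Two SD assumptions were used: the two-group SD of 1.41; and SD 1.7 in both dose arms with 1.04 in placebo, which pools to √((2 × 1.7² + 1.04²)/3) = 1.51 and is used as a common value.

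| SD | n per group | λ, midway / extreme | Power, midway / extreme |
|---|---|---|---|
| 1.41 | 30 | 13.97 / 18.63 | 92% / 97% |
| 1.41 | 27 | 12.57 / 16.77 | 89% / 96% |
| 1.51 | 30 | 12.13 / 16.17 | 88% / 95% |
| 1.51 | 27 | 10.92 / 14.56 | 84% / 93% |

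**Step 5: pairwise comparisons.** These are noncentral-t powers for a 1.36 cm difference and SD 1.41.

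| Two-sided alpha | 30 per group | 27 per group |
|---|---|---|
| 0.05 (one comparison) | 96% | 94% |
| 0.025 (two doses against placebo) | 92% | 89% |
| 0.0167 (all three pairs) | 89% | 85% |

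For 80% power, the second row needs 21–22 per group and the third 23–24, both below 30.

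**The case against.** The strongest reply is that nothing of substance is wrong. The figure of 30 per group follows exactly from the plan's own inputs if the base is left at 16.85 or rounded to 17, so 18 and 30 may be a t-based and a normal-approximation rounding of one calculation. The gap from the printed rule is one or two women per group; going from 30 to 32 moves single-comparison power only from 95.7% to 96.7%. The √3 factor, however poorly founded, errs on the generous side here. The budget ceiling and the 10% dropout are openly disclosed as limitations.

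Most of this stands. In particular, a reader might infer from the arithmetic slip and the missing inflation that the trial is underpowered or needs 96 or 105 women. The document does not support that. The stated target is 80% power, and every scenario tabulated above exceeds it even with 27 completers. Nor can one reject the √3 rule and then count failure to reach 31.2 as a shortfall.

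The reply does not remove the reporting fault. That 18 and 30 come from two roundings is a plausible guess the document does not confirm, and no single printed base gives both. Disclosing a cap and a dropout ceiling is not the same as stating the power they leave. The square-root factor remains tied to no comparison or error rate.

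**Conclusion.** The point holds as a correction to the stated figures. The printed rule gives 31.2 per group (32 after rounding, 96 in total) against a stated 30 and 90. The multiplier does not deliver a stated power for the planned three-group test, and the accepted dropout is outside the calculation. The power of the planned design is consequently missing, although it can be computed from the inputs given.

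The validity of the trial is not threatened and no extra women are needed. Power for the planned test is about 92–97% at 30 and 89–96% at 27 per group with SD 1.41, or about 88–95% and 84–93% with the pooled SD of 1.51.

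These results rest on the plan's own 1.36 cm difference and SDs, two-sided alpha, and complete data on those counted as evaluable. They say nothing about 2000 IU against 4000 IU. Because the Discussion speaks of presenting the best dose, a reader might conclude that this contrast is underpowered. The protocol assumes no dose-to-dose difference, so that cannot be established. Purely as illustration, half the planning effect (0.68 cm, my assumption) would have about 45% power at 30 per group, with SD 1.41 and alpha 0.05.

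**What to change.** Keep 90 women and rewrite the sample size paragraph:

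- Reconcile 18 with 30 by showing the base actually used and how it was rounded.
- Delete the multiplication by the square root of the number of groups.
- Say in this section, as the limitations already do, that 90 is limited by budget.
- State the power for the planned analysis at 30 randomised and 27 evaluable per group, with its assumptions.

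Possible wording:

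*The number of women is limited by budget to 90 (30 per group), leaving 27 evaluable per group after 10% dropout. For a 1.36 cm difference between the highest and lowest group means in 12-week waist change, the three-group time-by-group test at alpha 0.05 has about 92–97% power with 30 and 89–96% with 27 per group (common SD 1.41 cm), or about 88–95% and 84–93% if the SD is 1.7 cm in both dose groups and 1.04 cm in placebo. The range depends on whether the 2000 IU mean lies midway or at either extreme.*

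If dose-versus-placebo comparisons at two-sided alpha 0.025 are added to the Statistical analysis section, their power can be given too: about 92% at 30 and 89% at 27 per group with SD 1.41. It should not stand alone, because that section does not currently plan those tests.

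Cost: one reworded paragraph, with no change to recruitment, allocation or the planned analysis.
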